### Plans to promote participant retention and complete follow-up {18b}

Our sample size calculation allows for an attrition rate of 15%; however, this is a conservative estimate, with the attrition rate being 10% in our pilot trial. To promote retention, participants are sent a thank you card at 4 months and 11 months post-randomisation as an expression of appreciation for their contributions to the project and are additionally given £20 in acknowledgement of their time at each research assessment (£60 in total, or £40 total for participants who only receive an 8-month follow-up assessment). Participants who take part in one of the optional qualitative interview studies on their experiences of therapy will receive a further £20 for their time. All participants also receive an allocation call from a clinically qualified member of the trial team which, in addition to providing opportunities to explore their responses to allocation, allows them to be asked for their feedback on the assessment process and promote retention by refining future contact to align with their preferences.

In order to offer a person-centred assessment approach and facilitate engagement, flexibility, and participant choice, RAs receive pre-trial training delivered by both a clinician and lived experience expert which centres on minimising burden and ensuring appropriate care and encouragement throughout the assessment process. RAs follow a standardised protocol for managing distress, and participants are additionally offered a wellbeing check-in call after assessments to provide an opportunity for emotional support, as well as the Chance to offer feedback and express a preference for how they may like future follow-ups to be conducted. A 2-month window is utilised for follow-ups to maximise available outcome data and participants are contacted in advance of their follow-up due date and provided with contact options (e.g. the opportunity to conduct the assessment over the telephone or over video call instead of face to face, or meeting for shorter appointments spread across multiple occasions) to minimise burden and promote retention into the trial. The complete battery of assessment measures (as listed in section “Plans for assessment and collection of outcomes {18a}”) will be administered to all participants willing to complete them. This also applies to participants who have discontinued or withdrawn from the intervention or whose individual intervention has deviated from the intervention protocol. RAs work within an assertive outreach model, offering participant choice about the timing and location of appointments in addition to ordering outcome measures in priority, reiterating choices to decline questions/measures, and ensuring adequate breaks are taken as required. RAs discuss follow-ups at weekly trial management supervision to promote problem solving for participant retention issues that arise, and these are also discussed at site meetings and the TMG to share cross-study learning.

### Data management {19}

Participant research data are collected and stored only after the informed consent process is complete. All research assessment data are stored separately to personally identifiable data, and each participant is provided with a unique trial identification number that is written on all assessment forms and relevant datasheets and databases. A registration record linking patient identity, contact details and trial identification number is kept electronically at each site and stored securely, with access granted only to authorised users as per the delegation log. Paper data for participants (i.e. research assessment measures for baseline, 8- and 14-month follow-up) are stored securely in locked cabinets on approved NHS and University premises, whereas electronic data are stored on approved NHS or University drives. All data are kept in accordance with General Data Protection Regulation, with paper research assessment measures inputted on a web-based electronic data capture system (InferMed MACRO version 4; KCTU), which is compliant with GCP guidelines and hosted on a dedicated server within KCL.

RAs are expected to enter data onto MACRO within 1 week of the research assessment. Functionality on MACRO includes the use of range checks for specific data fields to reduce the risk of entry errors, as well as missing data codes programmed into fields for ease of analysis. To aid monitoring, the system is also programmed to flag when a missing data code is entered. Role-specific logins and training for MACRO further increases the usability and ability to monitor and audit data entry, with no data inputted or amended independently of the study site responsible for entering the data. Data entered from paper source worksheets completed at sites will also be checked against electronic data for accuracy; to date, initial site audits conducted in spring 2024 included an accuracy check of all baseline primary outcome data and all data from one mechanisms outcome measure currently available at the site. Accuracy will be further checked for 100% of the primary outcome for all baseline data across all sites. If the error rate is greater than 1% accuracy checks for all data will be triggered.

To protect the blind, a separate MACRO database is used to capture therapy attendance and AE data. Trial therapists and RAs also input data into site-specific NHS clinical records systems, including progress notes for research and/or therapy appointments and letters. A copy of the participant’s consent form is additionally uploaded onto their NHS clinical record, with researchers’ use of clinical record systems stipulated as part of the informed consent process. The statistical staff at KCTU will have access to the final trial dataset, and after the main publication the CIs, co-investigators, and trial manager will likewise gain access. In accordance with the sponsor’s Information Governance procedures, the retention period after the end of the study is 5 years for consent forms and research management documents, whereas data will be retained for 5 years after the primary publication.

### Confidentiality {27}

All personally identifiable information (PID) for participants is password protected and securely stored on NHS or University drives with access granted only to authorised members of the research team. Paper copies of assessment materials are pseudo-anonymised with a Participant Identification Number and stored in secure NHS or University premises separate to PID. Participants are informed of the security and confidentiality of their data, including the mandated limits to confidentiality in the event of researchers being provided with information that indicates the participant or another person is deemed to be at risk. Audio recordings are conducted in a manner consistent with NHS policies and procedures at the individual site, then transferred to a secure NHS drive which are accessible only to members of the research team with assigned responsibility, as per the study delegation log. Further, all qualitative interviews will be transcribed by members of the research team with any identifying information (e.g. names, places) removed.

### Plans for collection, laboratory evaluation, and storage of biological specimens for genetic or molecular analysis in this trial/future use {33}

No biological specimens will be collected as part of the trial.

## Statistical methods

### Statistical methods for primary and secondary outcomes {20a}

A detailed SAP is in preparation and will be approved by the TMG, DMEC, and TSC prior to publication on the ISRCTN registry.

We will report participant flow using the CONSORT 2018 extension for social and psychological intervention trials [70]. Assessment of recruitment, drop-out, and completeness of therapy will be summarised by descriptive statistics. The primary analyses will use the intention-to-treat population to estimate the treatment policy estimand. The intention to treat population will consist of all participants randomised, analysed in the arms to which they were randomised, regardless of treatment switching. Statisticians will be unblinded after database lock as the statistical analysis needs to account for therapist effects in the TWV arm.

To test the primary hypothesis, we will fit a linear mixed model to the repeated measures of the QPR at 8 and 14 months, with fixed effects of randomisation, time, time by randomisation interaction, site, diagnosis, and baseline QPR, and random effects for participants and therapist. The treatment policy estimand will be estimated as the adjusted between-group mean difference from the model for each timepoint separately. All hypotheses for secondary outcomes will be analysed using linear mixed models for continuous outcomes and logistic mixed models for binary outcomes.

To test treatment-effect mechanisms, mediation analysis will use parametric regression models to estimate the indirect effects of TWV on the mechanism measures and of mechanisms on primary and key secondary outcomes, if an effect is found. Results will be reported using A Guideline for Reporting Mediation Analysis (AGrEMA) guidelines [71].

### Interim analyses {21b}

No interim analysis is planned.

### Methods for additional analyses (e.g. subgroup analyses) {20b}

Any pre-specified subgroup analyses will be detailed in the SAP before analysis is undertaken.

### Methods in analysis to handle protocol non-adherence and any statistical methods to handle missing data {20c}

Maximum likelihood estimation will allow for missing outcome data under a missing-at-random assumption, conditional on the covariates in the model.

### Plans to give access to the full protocol, participant-level data, and statistical code {31c}

The final trial dataset and statistical code will be held and managed by KCTU, and reasonable requests for access to the dataset and statistical code will be considered in the first instance by the CIs and the TMG and then KCTU.

#### Qualitative analysis

All data will be analysed using Thematic Analysis in accordance with the process outlined by Braun and Clarke [72]. Thematic Analysis is a flexible qualitative method in which verbatim transcriptions are systematically and iteratively coded line-by-line, with codes compared, contrasted and amalgamated to develop detailed themes describing patterns in participants’ experiences. Negative case data (i.e. that which is contradictory to other themes) will also be sought and described where possible. Data management and analysis will be supported by Microsoft Excel software. We will take a critical realist position, and data will be coded at a manifest level (i.e. analysing only the immediate meaning of participants’ language) to produce an accessible body of coded data from which meaningful thematic representations of participants’ perspectives can be reported.

To achieve our objectives of exploring mechanisms of action for TWV, participant interviews will be analysed to investigate the mechanisms by which the intervention is perceived to operate. Here we will employ an inductive approach whereby the researchers will not impose a pre-existing theoretical framework but will seek to identify and code data that offer relevant information about how participants experience or perceive the intervention to have impacted on their mental health, voice-hearing experiences, and personal recovery, and to draw patterns across participants’ experiences.

Analysis of the interviews with therapy participants will be conducted by independent researchers who do not work on the main trial and overseen by members of the TWV team, including those with lived experience of hearing voices. The therapist focus group will be chaired by a lived experience NHS worker, then analysed by members of the trial team (EL, AB and WJ), all of whom have lived experience of hearing voices. Participants in all three qualitative studies may be approached again once an initial analysis has been completed to provide feedback, with additional member checking [73] conducted with trial staff and lived experience consultants to enhance the trustworthiness and transparency of the final analysis.

## Oversight and monitoring

### Composition of the coordinating centre and trial steering committee {5d}

GMMH NHS Foundation Trust is the study’s primary sponsor. The daily running and organisation of the trial is coordinated by a central management team comprised of the CIs, the trial manager and the clinical lead, with site management overseen by PIs. The central management team meets on a weekly basis, with an additional TMG meeting convened monthly which is attended by the central management team, PIs, and co-investigators, including a lived experience researcher. PIs additionally hold regular team meetings with the RAs and therapists at the specific site (with appropriate measures for avoiding blind breaks); the trial manager also attends these meetings according to site requirements approximately once per month to ensure central management presence and support.

The TSC is comprised of an independent chairperson, a statistician with expertise in medical statistics, a clinician with expertise in psychological interventions for SMHP, and a lived experience representative, with both CIs and the trial manager also attending as non-independent members. Prior to each meeting, all TSC members are required to report any competing interests. The TSC’s role is to provide supervision and oversight of the project on behalf of the sponsor and funder, and to ensure the project is run in accordance with GCP and UK Policy Framework for Health and Social Care standards. It convenes biannually, with meetings scheduled approximately one fortnight following the DMEC to ensure recommendations from the latter are duly considered. The funder is provided with the minutes from both TSC and DMEC meetings, along with a summary of the committee’s suggestions and any actions taken. In this regard, both the TSC and DMEC additionally reviewed internal pilot data against the a-priori progression criteria (Table 3) in order to make appropriate recommendations to the funder.

**Table 3 Tab3:** Talking With Voices internal pilot progression criteria

**Threshold**	**Red**		**Amber**		**Green**	
	**%**	**(*****N*****)**	**%**	**(*****N*****)**	**%**	**(*****N*****)**
Trial recruitment	≤ 59	(≤ 97)	60–99	(98–162)	100	(163)
Recruitment rate per month	≤ 59	(≤ 8)	60–99	(9–14)	100	(15)
Number of sites opened	≤ 50	(≤ 2)	70	(3)	100	(4)
Proportion receiving allocated intervention	≤ 59	(≤ 48)	60–99	(49–81)	100	(82)
Proportion with complete primary outcome data	≤ 84	(≤ 25)	85–99	(26–29)	100	(30)

### Composition of the data monitoring committee, its role and reporting structure {21a}

The DMEC is comprised of a chairperson, a statistician with expertise in medical statistics, and a clinician with expertise in psychological interventions for SMHP. All above members are likewise independent of the sponsor, funder, and trial team and are required to report any competing interests prior to each meeting. DMEC meetings are further attended by both CIs, the trial manager, and the trial statistician and convene biannually with an option for dealing with any arising issues between meetings via phone or email if necessary. Meetings focus on reviewing trial progress and accruing data, including recruitment, ethical issues of consent, retention, data quality (e.g. return rates, treatment compliance), the incidence of AEs and SAEs, and any other factors that might compromise the conduct, progress, and satisfactory completion of the trial. A copy of the DMEC charter is retained by the trial manager in the ISF and the DMEC is further required to provide advice on the overall conduct and progress of the trial to the TSC.

### Adverse event reporting and harms {22}

An AE is defined as any untoward medical occurrence for a participant which may or may not be deemed related to study procedures or interventions. AEs capture a broad range of unfavourable or unintended clinical indicators, including symptom or disease, abnormal laboratory results, traffic accidents, and on some occasions reported increases in psychological distress and incidences of self-harm. Close attention is paid to AEs which have a temporal relationship to a trial procedure or intervention session in order to assess potential relatedness to the trial. Consistent with Health Research Authority (HRA) guidance for a non-CTIMP (i.e. the trial is not a Clinical Trial of an Investigational Medicinal Product), an SAE is defined as an AE that either (1) results in death, (2) is life threatening, (3) requires hospitalisation or prolongation of existing hospitalisation, (4) results in persistent or significant disability or incapacity, (5) consists of a congenital anomaly or birth defect, or (6) is another important medical event deemed serious based on clinical judgement. SAEs are not inclusive of planned hospitalisations for pre-existing conditions, unless there is also a serious deterioration in health.

(S)AE data is collected and monitored for all participants from the time of their enrolment into the study (i.e. the time at which they sign and date the study consent form). Such data is collected via spontaneous reporting from participants or their care teams to RAs or trial therapists, and via checking electronic patient records for risk updates ahead of assessment or intervention sessions. We also capture potential (S)AEs related to the study procedures and intervention in our participant feedback questionnaire given to participants at the point of trial exit. As those allocated to the intervention arm have weekly contact with a trial therapist, we would expect to see a reporting bias whereby more events are recorded for those in the therapy condition compared to those in TAU. To address this, we employ a systematic approach to identifying any SAEs not already reported to study team members via screening all participants’ electronic patient records at the point of trial exit.

In accordance with the study SOP on (S)AE reporting, members of the trial team are expected to report all (S)AEs to the trial manager within 24 h of becoming aware of the event. These are then reviewed to determine severity, intensity, causality (relatedness), and expectedness in line with HRA guidance for classification of (S)AEs for non-CTIMPs. We use Medical Dictionary for Regulatory Activities (MedDRA) System Organ Class (SOC) categories to standardise reporting of (S)AEs. In view of the study population, these are categorised under the “Psychiatric Disorders” SOC into further subcategories of self-injury (not suicide), suicidal ideation with a behavioural component, suicide, voluntary psychiatric hospital admission, involuntary psychiatric hospital admission, and other psychiatric events. In the event of uncertainty about classification, guidance is sought from the CIs. Events deemed expected for the study population include psychiatric hospital admissions, self-harm, suicidal ideation with or without a behavioural component, acting on commanding voices, and psychological distress following trial assessments and/or psychological therapy. These events have been deemed expected for the study population based on commonly occurring (S)AEs from our pilot study, and from consultation with our oversight committees (DMEC and TSC).

All (S)AEs are reported and monitored at monthly TMG meetings and at each meeting of the DMEC. The chair of the DMEC will also be informed of any SAEs that are deemed possibly or probably related to trial procedures or intervention in between meetings. It has been agreed between the TSC and DMEC committees that in the event of a pattern or significant number of related SAEs, a different procedure of independent monitoring may be agreed upon. SAEs are reported by the trial manager or CIs to the study sponsor as soon as possible (typically within 24 h) and SAEs classified as both unanticipated and related to study procedures will be reported to the REC/ HRA within 15 calendar days. Such events will also be reported to the REC/HRA immediately (and no later than two calendar days) for incidents that indicate risk of imminent death, serious injury, or serious illness, and require prompt remedial action for other participants. The AE database was made available to the sponsor for audit purposes in spring 2024 and a report of all AEs will be made available to the sponsor on request. All AEs and SAEs are entered by the trial manager onto the unblinded therapy attendance MACRO database and are reported during DMEC meetings. These processes aim to provide independent scrutiny of (S)AEs at different levels throughout the duration of the trial. Within the trial’s outcome publication, we will report details of all events classified as AEs and SAEs, regardless of expectedness or relatedness to study procedures or intervention.

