**ASSESSMENTS**								
Demographics form	X							
PSYRATS-AH	X					X		X
QPR	X					X		X
TVAQ	X					X		X
Approve—Voices	X					X		X
BAVQ-R	X					X		X
PSYRATS-MMH	X					X		X
TALE	X							
PCL-5	X					X		X
BCSS	X					X		X
DES-II	X					X		X
VAAS-12	X					X		X
Treatment documentation form						X		X
Trial evaluation form*						X		X
Qualitative interviews (participants and therapists)						X	X	X
Adverse events**						X		X
Thank you card				X			X	X

*PSYRATS-AH* The Psychotic Symptom Rating Scales-Auditory Hallucinations [54], *QPR* The Questionnaire About the Process of Recovery [49], *TVAQ* Trauma Voice Associations Questionnaire [57], *Approve-Voices* the Approve-Voices questionnaire [58], *BAVQ-R* The Revised Beliefs About Voices Questionnaire [59], *PSYRATS-MMH* The Psychotic Symptom Rating Scales-Multimodal Hallucinations (unpublished measure), *TALE* Trauma And Life Events Checklist [60], *PCL-5* PTSD Checklist for DSM-5 [61], *BCSS* Brief Core Schema Scale [62], *DES-II* The Dissociative Experiences Scale-II [63], *VAAS-12* Voices Acceptance and Action Scale - Brief Version [64]

^*^The trial evaluation form is offered to participants at trial exit (i.e. at either the 8-month or 14-month follow-up assessment, depending on the time at which they were enrolled in the trial)

^**^Adverse events will be monitored at each time point, and at every intervention session for the TWV group

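### The protocol foresees over-recording of events in the TWV arm but corrects it for SAEs only, so non-serious AE counts by arm are biased towards an excess under TWV

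*Protocol article*

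**What the plan says.** Section {22} (Adverse event reporting and harms) gives two routine routes for AEs and SAEs. The first is spontaneous: "Such data is collected via spontaneous reporting from participants or their care teams to RAs or trial therapists". The second works "via checking electronic patient records for risk updates ahead of assessment or intervention sessions". An exit questionnaire adds events related to study procedures or the intervention.

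The section then recognises an imbalance. Since "those allocated to the intervention arm have weekly contact with a trial therapist", it states that "we would expect to see a reporting bias whereby more events are recorded for those in the therapy condition compared to those in TAU". The remedy follows at once: "we employ a systematic approach to identifying any SAEs not already reported to study team members", done by screening every participant's electronic record at trial exit.

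The footnote to Table 2 (Participant timeline {13}) sets the schedule: "Adverse events will be monitored at each time point, and at every intervention session for the TWV group". Trial design {8} allows up to 26 weekly sessions plus up to 4 boosters. For the outcome publication, section {22} promises that "we will report details of all events classified as AEs and SAEs, regardless of expectedness or relatedness to study procedures or intervention". The last paragraph of the Discussion makes the trial's implications for practice conditional on benefit with no burden of adverse effects.

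**The concern.** The bias is predicted for events in general, but the correction is limited to serious ones. Section {22} counts self-harm and increased psychological distress among AEs, and suicidal ideation and acting on commanding voices among expected events. Many of these can fall below the SAE threshold, where the exit screen need not find them. For a therapy that engages hostile voices directly, they are events that readers will look at closely.

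If they are tabulated by arm as collected, TWV is likely to look worse than it is. A reader could not tell a real increase in distress or self-harm from the effect of a therapist being there every week to hear about it. Analysis cannot repair this later, because events never captured in TAU cannot be recovered from the trial database.

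**Working it through.** The article states no AE rate, harm contrast or harm power, so there is no figure to reproduce. The check compares capture routes by arm, counts monitoring points, and then illustrates the size.

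**1. Routes by arm for non-serious AEs**

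| Route | TWV + TAU | TAU alone |
|---|---|---|
| Spontaneous report to a research assistant | yes | yes |
| Spontaneous report to a trial therapist | yes | no therapist |
| Record check before assessments | yes | yes |
| Record check before therapy sessions | yes | no sessions |
| Exit questionnaire (study-related events only) | yes | yes |
| Exit record screen | SAEs only | SAEs only |

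The two routes that differ both follow the therapy schedule. The exit screen is the one step designed to equalise the arms, and it does not reach non-serious AEs. In addition, the section on choice of comparators {6b} rules out liaison between researchers and care teams for TAU alone, except for emergent risk.

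**2. Scheduled monitoring points, if every session is attended**

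- By month 8, TWV: 26 + 1 = 27, or 26 + 4 + 1 = 31 with all boosters. TAU: 1.
- By month 14 (about 207 participants): 28 to 32 against 2.

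These are points at which AEs are monitored. The article does not say that participants are asked about AEs at each session.

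**3. Illustration of size**

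Recorded risk = true risk × detection, so recorded risk ratio = true risk ratio × (TWV detection ÷ TAU detection).

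Assumptions, none from the documents: the same true risk of at least one AE in both arms (30%, 50% or 70%); detection 0.9 in TWV; TAU detection at a fraction r = 0.9, 0.75 or 0.5 of that. From the document: 296 ÷ 2 = 148 per arm.

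At a true risk of 50%, TWV records 0.5 × 0.9 = 45.0%, or 148 × 0.45 ≈ 67 people. The last column is the chance that a reader's own two-sided 5% comparison of proportions would show an excess in TWV: Φ[(p₁ − p₂ − 1.96√(2p̄(1 − p̄)/148)) ÷ √((p₁(1 − p₁) + p₂(1 − p₂))/148)].

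| r | TAU recorded | People in TAU | Apparent risk ratio (1/r) | Chance of a nominal excess |
|---|---|---|---|---|
| 1 | 45.0% | 67 | 1.00 | 5% (either direction) |
| 0.9 | 40.5% | 60 | 1.11 | 12% |
| 0.75 | 33.8% | 50 | 1.33 | 51% |
| 0.5 | 22.5% | 33 | 2.00 | 99% |

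For r = 0.9, 0.75 and 0.5, the chances are 8%, 28% and 83% at a true risk of 30%, and 20%, 78% and about 100% at 70%.

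**4. Which readings survive the bias**

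If detection in TWV is at least that in TAU, the recorded ratio is at least the true ratio. A recorded ratio at or below 1 then points, within sampling error, to a true ratio at or below 1. A recorded ratio above 1 is ambiguous. A real benefit can also be hidden: with a true ratio of 0.75 and r = 0.75, the recorded ratio is 0.75 ÷ 0.75 = 1.00.

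**The case against.** The article promises only to report event details. It states no AE contrast or test, and the analysis plan and the standard operating procedure on AE reporting, which are not shown, may settle how AEs are tabulated and qualified. TAU capture is real: there are care-team reports, record checks before assessments and an exit questionnaire. A check for risk updates could well surface self-harm. The detection rates above are invented. And because the bias runs against the therapy, it is conservative for a claim of safety.

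Much of this stands, and it rules out several stronger readings that a reader might infer:

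- That the results will show a harm difference. They are only biased in that direction. A true reduction could offset it, and the pilot saw fewer SAEs under therapy (Feasibility study section).
- That AEs are asked about at 31 contacts against 1. The text says monitored, and describes spontaneous reporting.
- That the AE data cannot inform the burden question either way. The absence of an excess, despite a bias towards one, would be reassuring.
- That a planned test has an inflated error rate. No such test is stated.

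A further fair objection is that the clinical record is not a neutral source. Data management {19} says trial therapists write progress notes into NHS records, so a screen for non-serious events that did not filter these out would bring the imbalance back.

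What the objection does not remove is the gap itself. It lies in data collection, which the article describes together with its remedy, and the remedy is narrower than the bias it is meant to address.

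**Conclusion.** The concern holds in limited form. Non-serious AEs are captured on a denser schedule in TWV, and the stated correction does not reach them. Published by arm as collected, their counts are biased towards an excess in TWV.

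The size is unknown. Under the assumed detection ratios, the apparent risk ratio with no true difference runs from 1.11 to 2.00. These values show how the bias scales and are not estimates for this trial. The direction rests on the protocol's own expectation.

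The consequence is one-sided: an observed excess could not be read as harm, whereas no excess would still support the condition on adverse effects set in the Discussion. The matter concerns descriptive safety reporting and its interpretation. It does not touch the primary analysis or the sample size.

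**What to change.** 1. Record the source of each AE and SAE: therapy session, assessment or its preceding record check, care team, exit questionnaire or exit screen.
2. Base any between-arm AE comparison on sources common to both arms, namely the 8- and 14-month assessments with their preceding record checks, and the exit record screen.
3. Where feasible, extend the exit screen to non-serious events in the psychiatric subcategories that section {22} already lists. Exclude entries written by trial therapists. As those entries reveal allocation, staff outside the blind should do the extraction.
4. List session-detected AEs separately, without a between-arm contrast, and state the ascertainment bias beside them.

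This costs a longer extraction form, one source field in the AE log and some wording in the analysis plan. Recruitment closed on 30 June 2025 with last visits due in January 2026, so some participants who have already left would need re-screening, subject to the withdrawal terms in section {11b}. The between-arm comparison will also contain fewer events. No new visits are needed. If re-screening proves impracticable, items 1 and 4 can still be done wherever the source can be established.
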